## Abstract

**Background:**

Prospective memory is important for our health and independence but declines with age. Hence, interventions to enhance prospective memory, for example by providing an incentive, may promote healthy ageing. The neuroanatomical correlates of prospective memory and the processing of incentive-related prospective memory changes in older adults are not fully understood. In an fMRI study, we will therefore test whether incentives improve prospective memory in older adults and how prospective memory is processed in the brain in general, and when incentives are provided. Since goals and interests change across adulthood, avoiding losses is becoming more important for older adults than achieving gains. We therefore posit that loss-related incentives will enhance prospective memory, which will be subserved by increased prefrontal and midbrain activity.

**Methods:**

We will include *n* = 60 healthy older adults (60–75 years of age) in a randomized, single-blind, and parallel-group study. We will acquire 7T fMRI data in an incentive group and a control group (*n* = 30 each, stratified by education, age, and sex). Before and after fMRI, all participants will complete questionnaires and cognitive tests to assess possible confounders (e.g., income, personality traits, sensitivity to reward or punishment).

**Discussion:**

The results of this study will clarify whether loss-related incentives can enhance prospective memory and how any enhancement is processed in the brain. In addition, we will determine how prospective memory is processed in the brain in general. The results of our study will be an important step towards a better understanding of how prospective memory changes when we get older and for developing interventions to counteract cognitive decline.

## Background

Prospective memory is the ability to remember doing something at a specific point in time in the future (i.e., time-based prospective memory) or when a specific event occurs (i.e., event-based prospective memory) [1]. Whether brain regions involved in time-based and event-based prospective memory overlap or differ is hardly understood, particularly when it comes to ageing. Most neuroimaging studies in older adults tested event-based prospective memory using fMRI but not time-based prospective memory [2–6]. One study that did assess both types of prospective memory reported that network activity was similar as both tasks activated frontal and parietal brain regions, the insula, and the thalamus [4]. The time-based task in that study, however, was very similar to an event-based task since a clock was always in plain view so the participants did not need to remember the time-based intention by themselves. Instead, they were reminded by an external cue (i.e., the clock) which was constantly visible. Therefore, it could be that brain activity was similar in both tasks just because the task setup was very similar. It would be important to test whether older adults activate other brain regions when they need to remember time-based intentions by themselves [1, 7, 8]. This would help determine whether ageing affects time-based and event-based prospective memory differently in the brain.

Remembering prospective intentions is important for maintaining health and independence in older adults (e.g., remembering to meet a doctor or to take medication at a specific time) [9, 10]. Finding ways to improve or facilitate prospective memory may therefore promote healthy ageing. Motivation influences how well people encode and retrieve memories [11]. Enhancing motivation, for example by providing incentives, may thus be a way to improve prospective memory. Whether and how incentives influence prospective memory in older adults is not fully understood. There is evidence to suggest that event-based prospective memory can be improved when incentives include a prosocial component (i.e., a donation) [12]. This might be particularly motivating for older adults since they are usually more empathic and thus, more prosocial [13]. In addition, there is evidence to suggest that goals and interests change across adulthood [14], with avoiding losses becoming more important for older adults than achieving gains [15]. This is supported by an event-based prospective memory study, in which older adults performed better when they tried to avoid financial losses rather than to achieve financial gains [12]. It would be important to complement insights gained from event-based prospective memory with what happens to time-based prospective memory when losing an incentive was to be avoided. Prospective memory failures in daily life are often followed by financial losses (e.g., forgetting to pay a bill on time or forgetting to return a rented item on time may lead to financial extra charges). A better understanding of the consequences that follow prospective memory failure would therefore help to discern the mechanisms involved in motivational processes of prospective memory. In addition, we know nothing about incentive-related processing in the brain when prospective memory tasks are used. In other cognitive domains, such as decision making, the monetary incentive delay task has often been used to investigate incentive-related processing in the brain [16–18]. It has been found that younger adults activate a fronto-striatal-thalamic network during anticipation of an incentive, regardless of whether they try to achieve gains or to avoid losses [19]. Older adults, in contrast, activate the lateral prefrontal cortex in addition to midbrain areas and the insula [18]. It would be important to test whether these differences in older adults’ activity patterns are specific to the monetary incentive delay task or whether they can be generalised to prospective memory tasks.

The aims of the current study are, therefore, threefold. First, we investigate the functional neuroanatomy of prospective memory with a particular emphasis on the question whether brain regions involved in time-based and event-based prospective memory overlap or differ. We expect them to differ when using a time-based prospective memory paradigm in which participants actively align their intentions with time. Second, we test whether event-based or time-based prospective memory can be modulated when participants have to avoid losing an incentive. We hypothesize that this will improve prospective memory. Third, we investigate the neuroanatomical correlates of incentive-related processing during prospective memory tasks. We expect increased prefrontal and midbrain activity when participants avoid losing an incentive and that the strength of activity increase will be associated with prospective memory task performance.

## Methods and design

### Participants eligibility and recruitment

In this randomized, single-blind, and parallel-group study, *n* = 60 healthy older participants (60—75 years of age) will be included. Inclusion criteria will be fluency in German, no evidence of cognitive impairment on the Cognitive Telephone Screening (COGTEL; [20]), normal or corrected-to-normal vision and no clinically relevant depressive symptoms according to the Geriatric Depression Scale (GDS) (i.e., total score ≤ 5) [21]. Exclusion criteria will be past head injuries, permanent make-up, metal implants above the hips, any history of neurological or psychiatric disease, current or lifetime alcohol or drug abuse, intake of psychotropic drugs, brain damage, as well as magnetisable implants (e.g., cardiac pacemaker, brain stimulator). All participants will provide written informed consent before testing. Recruitment will be done via newspaper or Facebook advertisement. The study has been approved by the Ethics Committee of the Canton of Bern (Switzerland) and will be conducted according to the Declaration of Helsinki.

### Screening and group allocation

Participants will be screened over the telephone and only be invited to take part in the study if deemed eligible. Included participants will be assigned to one of two groups that will either receive an incentive during prospective memory tasks or not. Groups will be allocated using computer-generated random numbers, stratified by education, age, and sex.

### Study procedure

The study will consist of an online assessment of possible confounding factors using reliable and valid questionnaires as well as an on-site visit (Fig. 1). All participants will provide information on their monthly income, retirement status, monetary satisfaction and how often they donate money to charity. In addition, we will use the Edinburgh Handedness Inventory (EHI; [22]) to assess handedness and the NEO- Five Factor Inventory (NEO-FFI; [23]) to assess personality traits. To assess general sensitivity to reward or punishment, we will use the Behavioural Inhibition System/Behavioural Activation System Scales (BIS/BAS; [24]). Finally, to assess everyday prospective memory abilities, we will use the prospective and retrospective memory questionnaire (PMRQ; [25]) and the metacognitive prospective memory inventory (MPMI; [26]).

**Fig. 1 Fig1:**
[figure not shown]
Study procedure

On the study date, we will acquire structural and functional MRI data using a 7-Tesla ultra-high-field Magnetom Terra scanner (Siemens Medical Systems, Erlangen, Germany). During fMRI, time-based and event-based prospective memory will be tested, followed by a modified version of the monetary incentive delay task (MID; [27]), which will be used to localize areas involved in incentive-related processing in general. In between the two fMRI tasks, resting state fMRI data will be acquired to allow participants to have a break before the next task. For task-based and resting-state fMRI, we will use a gradient echo sequence (TR = 1 s, TE = 24 ms, voxel size = 1.4 × 1.4 × 1.4 mm). T1-weighted anatomical images will be obtained using a MP2RAGE sequence (TR = 6 s, TE = 2.06 ms, voxel size 0.63 × 0.63 × 0.63 mm). We will acquire physiological data (i.e., heart rate and breathing) to control for noise [28].

After MRI data acquisition, we will ask participants to describe the prospective memory task in their own words to assess whether they remember what they had to do during the prospective memory tasks. Then they will rate the perceived importance, motivation, and difficulty of the tasks. Finally, they will complete a German vocabulary test to test their verbal intelligence [29] as well as the Trail Making Test [30] and the Digit-Symbol Substitution Test [31] to control for a possible influence of problems with executive functions.

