### Monetary incentive delay task

To examine the neural substrates of incentive-related processing in the absence of prospective memory, participants will complete a modified version of the monetary incentive delay task [27, 35] that consists of a baseline and an incentive block.

At baseline, the participants will need to respond as fast and correctly as possible to triangles or squares and they will receive feedback (i.e., green tick = correct, red cross = incorrect or too late). Each trial will start with a fixation cross presented in the centre of the screen for 0.6—1.0 s. Then, either of the two stimuli will appear for 0.8 s, followed by another fixation cross (for 1.0—1.4 s) and feedback (for 0.5 s). After 20 trials, the mean response time of all correct answers will be calculated. Next, the incentive block will follow, during which the participants will again respond to triangles or squares (Fig. 3). In contrast to the baseline condition, however, they will be told that for some trials, it would now be possible to keep or lose an incentive. Each trial will start with the presentation of a fixation cross in the centre of the screen for 1—1.5 s, followed by a magnitude incentive cue for 2 s, and another fixation cross for 2—2.5 s. Then, participants will have to respond again to triangles or squares and, after another fixation cross, they will again receive feedback. The magnitude incentive cue will either be an empty white circle indicating a control trial, or a white circle with one horizontal line indicating an incentive trial. The two magnitude incentive cues will be presented 40 times each in randomized order. Hence, participants will complete a total of 80 trials. In order not to lose money, participants will need to answer correctly and faster than their mean response time during baseline. Control trials will be similar to the baseline condition. For incentive trials, answers that were correct and faster as during baseline will be indicated by a centime coin. A lost point (i.e., reaction time was slower than during baseline or an incorrect answer was given) will be indicated by a centime coin with a red cross. Below any 50-cent coin, the cumulative points will be shown. Participants will initially be endowed with an amount of 20 Swiss francs (40 points, each point corresponds to 0.50 Swiss Francs) and will be informed that they may lose it, depending on their response. We will encourage participants to respond as quickly as possible regardless of the type of the incentive cue. Comparable to previous studies, participants will have to keep more than 60% of total points (i.e., 24 points) to finally earn the incentive [27]. Otherwise, they will lose all the money. Again, half of their earnings will be donated to an organization of their choice.

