### Statistical analysis

#### Behavioural: Do loss-related incentives enhance prospective memory?

Since we are primarily interested in whether incentives will enhance prospective memory, we will report accuracy and mean response times for the event-based task as well as accuracy and clock checking for the time-based task as primary outcomes.

First, we will test whether incentives will improve task accuracy. We will use two-way mixed-design ANOVA on correctly remembered trials, with the within-subject factor ‘task type’ (event-based or time-based) and the between-subject factor ‘group’ (incentive or control). Next, we will test whether response times in the event-based task will become quicker with an incentive. We will use one-way ANOVA on response times for correctly remembered trials, with the between-subject factor ‘group’ (incentive or control). For time-based prospective memory, we will test whether an incentive influences how often participants check the clock. Similar to our previous study [36], we will divide the 30 s before and after each target time into four intervals: T – 30 refers to the interval 30 to 15 s and T – 15 to the interval 15 to 0 s before target time. T + 15 or T + 30 then correspond to the intervals 0 to 15 s and 15 to 30 s after the target time. We will use a two-way ANOVA with the within-subject factor ‘time-interval’ and the between-subject factor ‘group’ (incentive or control). Finally, we will test whether monthly income, retirement status, personality traits, reward sensitivity, executive functions, or daily life prospective memory will predict performance. We will use linear regression with prospective memory accuracy as dependent variable and scores from the questionnaires as predictors. Age and gender will be included as covariates in all statistical analyses.

We will use R (Version 4.2.1) with Rstudio (Version 2022.02.3) for statistical analyses, with *p* < 0.05 considered statistically significant. We will correct for multiple comparisons using Tukey’s method. Whenever the assumptions of normality or homogeneity are not met, data will be transformed and/or non-parametric alternatives will be used. In case of missing data, we will use linear-mixed effects models rather than ANOVAs.

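### Executive-function scores meant as controls are taken after the incentive and the outcome, while the pre-allocation COGTEL score has no stated analytic use

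*Protocol article*

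**What the plan says.** All references are to the protocol article.

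- **Order of the visit (Study procedure).** "During fMRI, time-based and event-based prospective memory will be tested, followed by a modified version of the monetary incentive delay task". The incentive operates within the prospective memory tasks. After scanning, participants recall and rate the tasks, and then: "Finally, they will complete a German vocabulary test to test their verbal intelligence [29] as well as the Trail Making Test [30". The Digit-Symbol Substitution Test is given at the same point. The purpose is "to control for a possible influence of problems with executive functions".
- **Abstract, Methods.** "Before and after fMRI, all participants will complete questionnaires and cognitive tests to assess possible confounders". It does not say which cognitive test comes before the scan. The only cognitive test that the body of the article places earlier is the telephone screen.
- **COGTEL (Participants eligibility and recruitment; Screening and group allocation).** One inclusion criterion is "no evidence of cognitive impairment on the Cognitive Telephone Screening (COGTEL; [20". Screening is by telephone and precedes assignment. The stratification factors are education, age and sex. No other use of the COGTEL score is mentioned.
- **Analysis (Statistical analysis, Behavioural).** The group comparisons are ANOVAs on accuracy, event-based response time and clock checking. Age and gender are the covariates named for every analysis. A separate linear regression follows: "Finally, we will test whether monthly income, retirement status, personality traits, reward sensitivity, executive functions, or daily life prospective memory will predict performance". Its dependent variable is prospective memory accuracy. Neither group nor COGTEL nor vocabulary is among the listed predictors.

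**The concern.** The purpose given to the executive tests and the time at which they are taken do not fit together. A score can serve as a baseline confounder only if neither the randomised condition nor the outcome could have affected it. Trail Making and Digit-Symbol are speeded and depend on effort. They follow the incentive, the outcome itself, a long scan and the monetary incentive delay task. If the incentive or success on the task changes effort afterwards, the scores carry part of what is being studied.

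Two things are at stake. First, adjusting the incentive effect for such a score could remove part of that effect. In the predictor regression, an association could reflect performance or incentive acting on the later test, not executive function acting on performance. Second, a cognitive measure taken before allocation exists and is free of this difficulty, but the analysis section gives it no role.

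**Working it through.** The plan states no figure on this point, so there is none to reproduce. The check compares timing with use and then sizes the consequences on assumed values.

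**1. Timing against use**

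| Measure | Taken | In group ANOVAs | In predictor regression |
|---|---|---|---|
| COGTEL | before allocation | not named | not named |
| Trail Making, Digit-Symbol | after incentive and outcome | no | yes, as executive functions |
| Vocabulary | after incentive and outcome | no | not named |
| Age, gender | fixed at entry | yes | yes |

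The post-scan scores enter one place only, the regression. The bias in the planned group ANOVAs from the timing of these tests is therefore zero.

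**2. If a group effect were adjusted for a post-scan score**

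This analysis is not specified; it is only implied by the wording about control. Let the true group effect be 0.50 SD (assumed), let the incentive shift the post-scan score by s SD, and let the within-group correlation with accuracy be r. The adjusted effect is 0.50 − r × s.

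| s | r = 0.2 | r = 0.3 | r = 0.5 |
|---|---|---|---|
| 0 | 0.50 | 0.50 | 0.50 |
| 0.1 | 0.48 | 0.47 | 0.45 |
| 0.2 | 0.46 | 0.44 | 0.40 |
| 0.3 | 0.44 | 0.41 | 0.35 |

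A simulation with 30 per group at s = 0.2, r = 0.3 gave 0.437, in agreement with 0.44.

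**3. The predictor regression**

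The listed predictors do not include group, so the two groups are pooled. With equal groups, the incentive alone adds 0.50 × s / 4 to the covariance of score and accuracy. If the within-group correlation is zero and s = 0.3, this is 0.0375. The pooled correlation is then 0.0375 / √(1.0625 × 1.0225) = 0.036. This route is small. The other route, in which each person's task experience affects later test effort, cannot be sized from the document.

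**4. What COGTEL could add**

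With partial correlation r between COGTEL and the outcome, given age and gender, residual variance falls by the factor 1 − r². The equivalent sample-size factor is 1/(1 − r²). Power is for a between-group difference of 0.5 SD, 30 per arm, two-sided 0.05, normal approximation: Φ(0.5 × √15 / √(1 − r²) − 1.96).

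| r (assumed) | Residual variance removed | 1/(1 − r²) | Power |
|---|---|---|---|
| 0 | 0% | 1.00 | 0.49 |
| 0.2 | 4% | 1.04 | 0.51 |
| 0.3 | 9% | 1.10 | 0.53 |
| 0.5 | 25% | 1.33 | 0.61 |

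**5. The price**

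With intercept, group, age and gender fitted to 60 participants, residual degrees of freedom go from 56 to 55. Chance imbalance in one further covariate inflates the variance of the group estimate by 27.5/27 = 1.019 on average (confirmed by simulation). At r = 0.2 the net factor is 0.96 × 1.019 = 0.98, and at r = 0.3 it is 0.91 × 1.019 = 0.93. Break-even is near r = √0.018 = 0.13.

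**The case against.** The strongest reply is that nothing planned for the incentive question is harmed. This stands. The ANOVAs name age and gender as covariates and contain no executive score. A reader might infer from the wording about control that the primary comparison is biased; the document specifies no such adjustment.

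A reader might also point to the monetary incentive delay task, where participants must keep more than 60% of the points and "Otherwise, they will lose all the money". But the article says that "participants will complete a modified version of the monetary incentive delay task [27, 35] that consists of a baseline and an incentive block", with no restriction to the incentive group. It can add fatigue or discouragement in both arms, but it is not itself a randomised difference. The randomised exposure is the 5 Swiss Francs per prospective memory task, and whether that moves later scores cannot be settled from the document.

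Nor does the article say that the COGTEL score is thrown away. It states no use beyond eligibility, and a condensed article may leave more to a fuller plan. Omitting an optional prognostic covariate is not an error in a randomised, stratified comparison.

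The gain can also be overstated. Only the partial correlation given age and gender counts. Eligibility truncates the COGTEL range, and accuracy rests on 10 cues per task with possible ceiling or floor effects. A person-level covariate entered as a main effect does not reduce the within-subject error for group by task or group by interval. A claim that COGTEL is worth up to 20 extra participants (60 × 1.33 = 80) would need r = 0.5 and would still not reach those interactions.

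What remains is the mismatch between purpose and timing, and an unused baseline score in a section that does list its covariates and predictors.

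**Conclusion.** The point holds in limited form. Trail Making and Digit-Symbol are post-exposure, post-outcome measures and cannot serve as baseline confounders. This affects the interpretation of the secondary regression and would affect any adjustment of the group effect, by 0.02 to 0.15 SD over the assumed range of s = 0.1 to 0.3 and r = 0.2 to 0.5. It would be nil if the incentive does not shift the scores. It does not bias the planned primary comparisons. Vocabulary is not a listed predictor and forms no part of the problem.

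Using COGTEL is a low-cost improvement, not the correction of an error. A realistic gain is a 4% to 9% reduction in residual variance, somewhat less after the cost of the extra coefficient, for between-group main effects only. The 25% figure is an optimistic upper bound. All correlations and shifts are assumptions. The recommendation also presumes that the COGTEL score itself was recorded, not only whether the criterion was met.

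**What to change.** In Statistical analysis, Behavioural:

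1. Add the COGTEL score from telephone screening as a prespecified covariate, next to age and gender, in the group analyses of accuracy, event-based response time and clock checking.
2. Add COGTEL to the predictor regression as the baseline cognitive predictor.
3. State that post-scan Trail Making and Digit-Symbol scores are descriptive or correlational and will not be used to adjust the group effect. Bring the purpose given in Study procedure into line with this.

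Do not move the tests now. Recruitment began in January 2022 and data acquisition is described as ongoing. A change would mix pre-scan and post-scan scores in one variable, tie test order to enrolment date, and place speeded tests directly before the primary outcome.

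The cost is a few lines of text and one degree of freedom per model, with no new data if the score was kept. The change should be dated before outcomes are compared by group.
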